# High versus low pneumoperitoneum PressUre for parenchymal transection in minimally invasive major liver surgery (PPULS)—a non-inferiority, multicenter, randomized, controlled trial

**DOI:** 10.1186/s13063-025-09269-9

**Published:** 2025-12-01

**Keywords:** Pneumoperitoneum, Minimally invasive surgery, Parenchymal dissection, Liver surgery, Intraoperative blood loss, CO_2_ embolism

## Abstract

**Background:**

Low pneumoperitoneum pressure (LPP) lowers the incidence of CO_2_ embolisms in minimally invasive liver resections (MILR), while higher pneumoperitoneum pressure (HPP) reduces intraoperative blood loss. This contradiction necessitates careful pressure management especially in major liver resections where intraoperative blood loss greatly impacts postoperative outcome.

**Methods:**

In this randomized non-inferiority trial, adults undergoing elective MILR for any indication will be recruited in alignment with inclusion and exclusion criteria. After given informed consent, eligible patients will be randomized to either low (≤10 mmHg) or high (≥14 mmHg) pneumoperitoneum pressure during parenchymal transection. Blood, peritoneal biopsies, and liver tissue will be sampled to evaluate intraoperative tissue damage. Sample size (*n* = 66 patients per group) is calculated based on the current literature. The primary study endpoint is intraoperative blood loss during the parenchymal transection phase. Secondary endpoints include CO_2_ embolisms, intraoperative tissue damage, operation time, morbidity, mortality, and duration of hospitalization.

**Discussion:**

Minimizing intraoperative blood loss in MILR is a clinically relevant problem, which greatly impacts the procedure’s safety and influences the patient’s morbidity and mortality. HPP, exerting counter pressure to the vascular pressure, serves for bleeding control in MILR. The risk of CO_2_ embolism, arising from the combination of high intra-abdominal pressure and low central venous pressure, favors the use of LPP. The proposed trial aims to assess the non-inferiority of LPP compared to HPP during the parenchymal transection phase of MILR.

**Trial registration:**

ClinicalTrials.gov NCT06770803. First Submitted: 2024-12-30, First Submitted that Met QC Criteria: 2025-01-07, First Posted: 2025-01-13.

**Supplementary Information:**

The online version contains supplementary material available at 10.1186/s13063-025-09269-9.

## Introduction

### Background and rationale {6a}

Minimally invasive techniques in liver surgery gain popularity as they facilitate postoperative recovery while achieving comparable oncologic outcomes to the open approach [1]. Since the first worldwide approval of the da Vinci® robotics platform in 2001, da Vinci®-assisted liver surgery has even further enhanced the application of laparoscopic surgery by implementing a three-dimensional view, the magnification of the operative field, and the seven degrees of freedom of the human hand, thereby overcoming the limitations of conventional laparoscopic surgery [2, 3]. No consensus on the application of pneumoperitoneum pressure in minimally invasive liver resections (MILR) has been reached yet, as prospective clinical studies are scarce. All minimally invasive techniques require carbon dioxide (CO_2_) for the induction and maintenance of the pneumoperitoneum, which can lead to the formation of CO_2_ embolisms potentially causing pulmonary edema, cerebral infarction, shock, and cardiac arrest [4]. In contrast, the positive pressure of the CO_2_ pneumoperitoneum reduces intraoperative blood loss during MILR alongside the development of new transection devices and advancements in inflow control [5, 6]. Intraoperative blood loss greatly impacts postoperative survival following liver surgery [7], and perioperative transfusions of packed red blood cells in oncologic liver resections represent an independent poor prognostic indicator for overall survival [8]. Low-pressure pneumoperitoneum on the other hand has been shown to decrease postoperative pain scores and analgesic consumption in comparison to standard pneumoperitoneum [9], and international guidelines recommend the application of “the lowest intra-abdominal pressure allowing adequate exposure of the operative field rather than a routine pressure” [10]. Nevertheless, evidence for the application of low-pressure pneumoperitoneum is only moderate to low, requiring additional studies to better define its safety [9]. MILRs are associated with an elevated risk of CO_2_ embolism due to the risk of rupture of the hepatic veins or exposure of the hepatic sinusoids. Luo et al. demonstrated in a recently published randomized controlled trial that a pneumoperitoneal pressure of 10 mmHg reduced the incidence and duration of severe CO_2_ embolisms during laparoscopic liver resection in comparison to standard 15 mmHg [11]. Additionally, low-pressure pneumoperitoneum was particularly beneficial to the subgroup of liver resections that were adjacent to the second hepatic hilum [11]. These results reinforce the correlation of the pneumoperitoneum pressure and the risk for CO_2_ embolisms. An additional advantage of low-pressure peritoneum is improved postoperative recovery [12]. No significant difference in intraoperative blood loss or the amount of blood transfusions was observed in the study by Luo et al., but 93.6% of all participants underwent minor and only 6.4% major resections [11]. An experimental study on piglets showed that high intra-abdominal pressure (16 mmHg) reduced bleeding in comparison to low pressure (8 mmHg) [13]. Other experimental, retrospective, and prospective comparative studies further strengthen the hypothesis that high pneumoperitoneum reduces blood loss [14].

To address this contradiction, we propose a randomized non-inferiority trial to compare low-pressure to high-pressure pneumoperitoneum during the transection phase of major MILR and its effect on intraoperative blood loss and the occurrence of embolic complications.

### Objectives {7}

The objective of this trial is to determine whether the maintenance of a low intraperitoneal insufflation pressure (IIP) of ≤10 mmHg during the parenchymal transection phase of conventional and robotic-assisted laparoscopic liver resections is non-inferior to a higher IIP of ≥14 mmHg in terms of intraoperative blood loss, gas embolisms, perioperative morbidity, and mortality.

The primary research question is as follows: Is the maintenance of a low IIP of ≤10 mmHg during the parenchymal transection phase of conventional or robotic-assisted laparoscopic liver resections non-inferior to a higher IIP of ≥14 mmHg in terms of intraoperative blood loss during the parenchymal transection phase?

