### Sample size {14}

The sample size calculation is based on the primary endpoint “intraoperative blood loss during the parenchymal transection phase.” A difference of 100 ml in blood loss is considered clinically relevant, setting the non-inferiority margin at 100. Assuming no difference in mean blood loss between the two groups and using a standard deviation of 184 for blood loss in minimally invasive major liver resection [20], the initial single-center sample size required to achieve 80% power (*β* = 0.2) at *α* = 0.05 was calculated as 42 per group. Adjusting for a multicenter study design with an intra-class correlation coefficient (ICC) of 0.05 across four centers, the required sample size increases to 66 patients per group. Accounting for a 5% loss to follow-up, we plan to include a total of 132 patients across both study arms.

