## Statistical methods

### Statistical methods for primary and secondary outcomes {20a}

The data will be managed and analyzed according to the applicable standard operating procedures (SOPs) within the shared unit of the clinical trial center. All relevant study information will be documented in case report forms (CRFs), which will be reviewed by the study team prior to data entry. A safety analysis will be conducted for all patients who underwent one of the interventions. Serious adverse events will be documented immediately, prompting notification of the principal investigator. Absolute and relative frequencies, as well as the severity and relationship to the intervention, will be compared between intervention groups.

The modified intention-to-treat (mITT) analysis will be used to evaluate the primary and secondary endpoints. The mITT set includes all randomized patients who initiated the intervention and met intraoperative inclusion criteria (e.g., exclusion of a PFO). Patients excluded intraoperatively due to contraindications (e.g., adhesions or peritoneal carcinomatosis) will not be included in the analysis.

The primary endpoint (intraoperative blood loss during the parenchymal transection phase) will be analyzed using linear regression if data follow a normal distribution. If normality is not met, a non-parametric bootstrap method will be employed to calculate confidence intervals. The 90% confidence interval (CI) for the mean difference between the two groups will be calculated, and the lower bound of this interval will be compared to the predefined non-inferiority margin of 100 ml to confirm non-inferiority. The corresponding *p* value will also be computed.

Secondary endpoints will also be analyzed:Continuous variables: These will be analyzed using descriptive statistics (mean, standard deviation, quartiles) along with two-sided 95% confidence intervals (CIs).Categorical variables: Absolute and relative frequencies will be reported, and two-sided *p* values will be calculated using the chi-squared test or Fisher’s exact test.

All statistical tests will be two-sided and conducted at a significance level of *α* = 0.05. Analyses will account for stratification to minimize bias and ensure accurate *p* values [22].

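### The objective claims non-inferiority on blood loss, gas embolism, morbidity and mortality, but the plan can decide it only for blood loss

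*Protocol article*

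**What the plan says.** All references are to the protocol article.

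- **Objectives {7}, first sentence:** the trial is to determine whether low pressure "is non-inferior to a higher IIP of ≥14 mmHg in terms of intraoperative blood loss, gas embolisms, perioperative morbidity, and mortality".
- **Objectives {7}, primary research question:** this is narrower. It asks only whether low pressure is "non-inferior to a higher IIP of ≥14 mmHg in terms of intraoperative blood loss during the parenchymal transection phase".
- **Sample size {14}:** "A difference of 100 ml in blood loss is considered clinically relevant, setting the non-inferiority margin at 100". No other margin appears in the article, and the patient number is derived from blood loss alone.
- **Statistical methods {20a}, primary endpoint:** a 90% confidence interval for the mean difference is compared with the 100 ml margin. This is the only non-inferiority rule.
- **Statistical methods {20a}, secondary endpoints:** for categorical variables, two-sided p "values will be calculated using the chi-squared test" or Fisher's exact test. Continuous variables get descriptive statistics with two-sided 95% confidence intervals.
- **Outcomes {12}:** embolism incidence, 30-day morbidity by the Comprehensive Complication Index, and 30- and 90-day survival are secondary endpoints.

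**The concern.** A non-inferiority claim needs a margin fixed in advance and a rule that compares an interval with it. Three of the four outcomes in the objective have neither. The tests named for the categorical ones address a different null hypothesis, that of no difference. Failing to reject that null does not show that low pressure is no worse by more than an acceptable amount, and in a trial sized for another endpoint such failure is the likely result even under real harm.

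At stake is the safety message. A reader of the final report who finds the stated objective beside non-significant p values for morbidity and mortality could conclude that non-inferiority had been shown. For embolism the framing is also awkward. The Abstract, Introduction and Discussion present fewer embolisms as the expected advantage of low pressure, so the natural question there is superiority.

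**Working it through.** **1. The plan's own number, to see what it covers.** Sample size {14} gives the margin (100 ml), the true difference ("Assuming no difference in mean blood loss between the two groups"), the standard deviation ("using a standard deviation of 184 for blood loss in minimally invasive major liver resection") and the result ("required to achieve 80% power (*β* = 0.2) at *α* = 0.05 was calculated as 42 per group").

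n per group = 2 × SD² × (z₁₋α + z₁₋β)² / margin²
= 2 × 184² × (1.645 + 0.842)² / 100² = 41.9, so 42 per group.

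This reproduces with one-sided α of 0.05, which matches the 90% interval in Statistical methods {20a}. The design effect with 42/4 = 10.5 patients per centre is 1 + (10.5 − 1) × 0.05 = 1.475. Then 42 × 1.475 = 61.95, so 62, and 62/0.95 = 65.3, so 66 per group, 132 in all. Every input is a blood-loss or design input. Embolism, morbidity and mortality do not enter.

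**2. Each outcome in the objective against what the plan provides.**

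| Outcome in the objective | Margin | Planned analysis | Can non-inferiority be concluded? |
|---|---|---|---|
| Blood loss, transection phase | 100 ml | 90% interval against the margin | Yes |
| Gas embolism (incidence) | None | Two-sided chi-squared or Fisher | No |
| Morbidity (Comprehensive Complication Index) | None | Descriptive statistics, 95% interval | No |
| Mortality (as a proportion) | None | Two-sided chi-squared or Fisher | No |

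**3. How often a difference test would miss real harm.** The article gives no morbidity or mortality rates, so those below are assumptions. With 66 per arm and two-sided 0.05, I summed the binomial probabilities of every pair of counts giving p ≥ 0.05 (chi-squared without continuity correction).

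| True rates, high v low pressure | Non-significant, chi-squared | Non-significant, Fisher |
|---|---|---|
| Binary complication, 20% v 30% | 74% | 80% |
| Mortality, 2% v 4% | 92% | 99% (98.5%) |
| Mortality, 2% v 6% | 80% | 93% |

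The complication row applies to categorical complications, not to the Comprehensive Complication Index.

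**4. What a real non-inferiority test would need.** With equal true rates p, 80% power and one-sided 0.05:

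n per arm = 2 × p(1 − p) × 6.183 / margin², where 6.183 = (1.645 + 0.842)² before rounding of the z values.

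- p = 20%, 10-point margin: 2 × 0.16 × 6.183 / 0.01 = 197.8, so 198.
- p = 30%, 10-point margin: 2 × 0.21 × 6.183 / 0.01 = 259.7, so 260.
- p = 2%, 5-point margin: 2 × 0.0196 × 6.183 / 0.0025 = 96.9, so 97.
- p = 2%, 10-point margin: 25. This fits within 66, but would accept mortality rising from 2% to 12%.

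The margins are illustrative, since the article states none.

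**5. Embolism as a superiority question.** The Discussion cites severe embolism of 67.1% at standard and 40.8% at low pressure. At those rates and 66 per arm, the planned two-sided test has power of about 81% (Fisher) to 86% (chi-squared), by the same enumeration.

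**The case against.** The strongest reply is that this is one loose summary sentence. The next sentence of Objectives {7} confines the primary question to transection-phase blood loss, and the Abstract, Outcomes {12} and Sample size {14} agree. The comparator rationale {6b} speaks only of evaluating embolism risk alongside blood loss. This stands in part: the primary conclusion and its sample size are untouched. It does not remove the mismatch, because the first sentence is the stated objective of the trial. Nor is it detail left to a separate analysis plan, since {20a} already fixes a different analysis for these endpoints.

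Four stronger readings are tempting, and the document does not support them.

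- A reader might infer that the trial intends to treat a non-significant p value as non-inferiority. Nothing says so; {20a} ties confirmation of non-inferiority only to blood loss and its margin. Misreading is a risk, not a plan.
- A reader might infer that all three remaining outcomes get difference tests. Overall morbidity is a continuous index and gets an interval, with no named test.
- A reader might infer that the embolism benefit goes untested. The two-sided test of incidence can already detect a reduction.
- A reader might infer that non-inferiority is simply the wrong hypothesis for embolism. A lower rate would also satisfy it, so it is weaker than the rationale warrants rather than wrong.

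The embolism power figures also need caution. By the article's own account the cited trial had 93.6% minor resections and graded embolism by the Schmandra test, whereas this trial enrols major or near-vascular resections and uses the Tübingen scale. The rates may not transfer.

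**Conclusion.** The point holds in limited form. The objective promises non-inferiority on four outcomes and the plan can deliver it on one. For embolism, morbidity and mortality there is no margin, no decision rule and no sample-size support.

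Under the assumed rates, non-significance at 66 per arm would be the usual result even with a true 10-point rise in a complication rate (74% to 80% of the time) or a doubling of mortality from 2% to 4% (92% to 99%). It would therefore carry little reassurance. These figures depend on the assumed rates and on all 66 per arm being analysed; with the planned 5% loss they would be slightly worse. The contradiction itself does not depend on them, and the blood-loss conclusion is not affected. It should be corrected, but it does not threaten the primary analysis.

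**What to change.** In Objectives {7}, restrict the non-inferiority objective to blood loss during the transection phase. List gas embolism, morbidity and mortality as secondary comparisons, each reported as a between-group difference with a 95% confidence interval. Describe embolism as a superiority (difference) question, which the planned two-sided test already addresses. In Statistical methods {20a}, add one sentence stating that a non-significant difference on a secondary endpoint is not evidence of non-inferiority.

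Optionally, embolism could be made a key secondary hypothesis tested only after non-inferiority on blood loss is shown. That is a reasonable choice, not the correction of an error.

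The cost is rewording, with no extra patients or data. The downside is that the non-inferiority claims for embolism, morbidity and mortality are given up. Keeping them would require justified margins and interval rules for each, and for most of the margins illustrated above more patients than planned.

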### Trial design {8}

This study is a two-arm parallel-group, randomized non-inferiority trial in patients undergoing elective minimally invasive liver surgery with an allocation ratio of 1:1 per hospital and a follow-up period of 3 months. The flow diagram of the study is presented in Fig. 1.

**Fig. 1 Fig1:**
[figure not shown]
CONSORT flowchart depicting the screening, enrollment, randomization, intervention, and follow-up assessments

## Methods: participants, interventions, and outcomes

### Study settings {9}

All patients being scheduled for elective conventional or da Vinci robotic-assisted laparoscopic liver resections for any benign or malignant indication will be screened for inclusion at the Department of General, Visceral and Transplant Surgery at Heidelberg University Hospital or collaborating hospitals.

### Eligibility criteria {10}

Inclusion criteria consist of:Age equal or older than 18 years.Capacity of consent.Planned elective conventional laparoscopic or da Vinci-assisted major liver resection or resections near the liver hilum or the hepatic venous vasculature. Major liver resections are defined as the resection of 3 liver segments or more (right and left partial hepatectomies, extended right and left hepatectomies, liver resections of 3 or more segments). Right posterior sectionectomies and mesohepatectomies of ≥2 liver segments are considered resections in proximity to the liver hilum or hepatic venous vasculature.

All study participants must give informed consent before study enrollment.

Exclusion criteria represent:The participation in another trial with interference of intervention of this studyBeing a woman who is pregnant or breast-feeding or planning to become pregnantAmerican Society of Anesthesiologists (AS) score >3Language barrierAny contraindication to a minimally invasive surgical approach or intolerance to pneumoperitoneumA patent foramen ovale (PFO) or any other structural cardiac defect that facilitates paradoxical gas embolismsDiagnosis of neuromuscular disease, heart failure NYHA > class II, or chronic obstructive pulmonary disease (COPD)Being on oral anticoagulation therapy other than aspirin 100 mg daily or any other condition known to increase the risk of bleeding

### Who will take informed consent? {26a}

A qualified physician, trained in the study protocol and consent procedures, will obtain informed consent. The physician will explain the study’s purpose and interventions, its potential risks and benefits, and the voluntary nature of participation. Written informed consent will be secured before any study procedures begin.

A model of the written informed consent form used in this study is provided as Supplementary File 1.

### Additional consent provisions for collection and use of participant data and biological specimens {26b}

The main informed consent form includes comprehensive information regarding the collection, storage, and future use of participant data and biological specimens. The form clearly outlines the types of data and specimens that will be collected, details the procedures for anonymization and secure storage, and describes any potential future research uses. By signing the form, participants agree to these terms as part of their overall study participation.

## Interventions

### Explanation for the choice of comparators {6b}

Evidence for the application of low-pressure pneumoperitoneum is only moderate to low. Therefore, we propose a randomized non-inferiority trial to investigate the effect of low-pressure in comparison to high-pressure pneumoperitoneum during the transection phase of major MILR on intraoperative blood loss during this phase while also evaluating the risk of CO_2_ embolisms.

### Intervention description {11a}

Intraperitoneal insufflation pressures (IIP) during the parenchymal transection phase of liver resection will be different between the two study groups. Baseline IIP of the surgical procedure will be ≤10 mmHg. IIP will be elevated to ≥14 mmHg in the intervention group during the parenchymal transection phase of liver resection, while IIP will be maintained at ≤10 mmHg in the control group. Deep neuromuscular blockade will be applied in all patients and is defined as a train-of-four (TOF) of 0 or posttetanic count of 1–2. The quality of the surgical field is rated every 8 min on the Leiden Surgical Rating Scale (L-SRS) during the transection phase and every 15 min outside of it. When the field conditions reach inadequate scores of ≤3, IAP will be increased accordingly in steps of 2 mmHg.

Pringle maneuver, the clamping of the hepatoduodenal ligament, is obligatory and predefined as a sequence of 20 min of clamping followed by 5 min of perfusion.

### Criteria for discontinuing or modifying allocated interventions {11b}

Individual withdrawal criteria will include the participant’s right to withdraw consent at any time without any negative consequences for their subsequent medical care. Participants may choose to withdraw if they experience adverse events or if they feel uncomfortable continuing in the study for any reason. Additionally, any significant changes in their medical condition that may affect their safety or the validity of the trial, such as newly diagnosed medical conditions or complications related to the surgical procedure, may also warrant withdrawal from the study. The research team will ensure that participants are fully informed of their right to discontinue their participation at any point during the trial, and efforts will be made to document the reasons for withdrawal if disclosed.

Withdrawal criteria for the overall PPULS trial may arise from significant changes in the safety landscape during the study period, such as emerging data that indicate an unacceptable level of risk for participants. This could include new findings related to the incidence of adverse events associated with the pneumoperitoneum pressures being tested, or if there are changes in clinical guidelines that recommend against the studied interventions. This trial will be discontinued only for reasons pertaining to efficacy, safety, or feasibility. However, at this stage, no specific overall withdrawal criteria have been identified; the study is designed with appropriate monitoring and safety protocols in place to ensure participant welfare throughout its duration.

